## 1. BACKGROUND INFORMATION AND RATIONALE

Medication non-adherence in patients with chronic cardiometabolic diseases is common, costly, and often underdiagnosed. Stroke, hypertension, heart disease, and diabetes account for over \$450 billion in healthcare expenditures annually in the US (Lum 2020). Within these disease states, rates of polypharmacy often exceed 65% contributing to a significant increase in risk for adverse drug events and drug-drug interactions (DDI). With the new Chronic Disease Management Test (CDMT), a non-invasive diagnostic test, the goal is to see if testing efficiently determines medication adherence and drug-drug interactions (DDIs) for patients with cardiometabolic multimorbidity, defined by the WHO as the coexistence of two or more chronic diseases in the same individual. This oral fluid-based test, produced by Aegis, detects and provides clinicians with adherence and DDI data on 150+ relevant medications across four major cardiometabolic conditions (coronary artery disease, heart failure, hypertension, diabetes, and COPD).

There are multiple reasons for poor medication adherence from those related to patients (e.g., suboptimal health literacy), to those that are related to physicians (e.g., medications prescribed by other physicians or being unaware about the patient’s adherence to prescribed medications), to those related to health care systems (e.g., limited access to follow-up care, absence of health information technology) (Brown 2013). Primary care providers absolutely must know whether their patients are complying with their prescribed medications to provide reliable and quality care. The factors that underlie non-adherence are underscored by how infrequently clinicians identify and diagnose nonadherence (Marcum 2013). DDIs are also unrecognized (Peabody 2018) and lead to non-adherence (Rugo 2021). All these factors signify a need for a simple, objective intervention that allows providers to recognize non-adherence and DDI (Marcum 2013). CDMT offers the advantage of a medication adherence assessment method that is accurate, valid, and sensitive to change. Furthermore, the CDMT has the ability to detect drug interactions when DDI testing is included, which leads to more non-adherence, drug toxicity, or loss of efficacy of the co-administered medication, and other medication-related problems. Accordingly, Aegis has approached one of the nation’s leading primary care models to determine whether VillageMD providers could change their practice in such a way that is beneficial to the most patients.

The measurement of patient medication adherence and use of interventions to improve adherence are rare in routine clinical practice. For this reason, medication adherence has been called the “next frontier in quality improvement” and is an important part of cardiovascular outcomes research (Ho 2009). With this study, we are providing objective and meaningful data that will provide a measure of medication adherence and assess the impact of non-adherence recognition in provider practice.

|             |                                                                                                                                                |                       |
|-------------|------------------------------------------------------------------------------------------------------------------------------------------------|-----------------------|
|             | Clinical Study Protocol                                                                                                                 |                       |
|             | Title: Measuring the Clinical Utility of Aegis’s Chronic Disease Management Test among VillageMD Providers: A CPV® Randomized Controlled Trial |                       |
| Supersedes: | Document Number:                                                                                                                               |                       |
|             | Effective Date:                                                                                                                                | Page: 13 of 25 |

This study is the third amendment to the ongoing QURE 3 study (approved on October 19th, 2021). The specific purpose of this study, hereon referred to as QURE Village, is to extend the findings of the original QURE 3 study and assess the clinical utility of the Chronic Disease Management Test (CDMT) at selected VillageMD clinics nationwide.

VillageMD is a national leader in primary care that focuses on improving chronic disease management. They devote 90% of resources to mitigating the effects of chronic conditions such as heart failure or chronic obstructive pulmonary disease (COPD).

In the original QURE 3 study protocol, which is described in more detail below, measured changes in prescribing practices using Clinical Performance and Value (CPV®) vignettes. the CPVs are a validated measurement tool that we used to demonstrate the enormous clinical variation in the management of chronic cardiometabolic diseases and with that we then assessed the impact of CDMT testing to improve physicians’ clinical decision-making.

We found from the baseline data collected, significant variation in how physicians managed cardiometabolic diseases. In cases where patients were experiencing symptoms of uncontrolled disease due to medication non-adherence, physicians failed to identify non-adherence as the etiology which led to an increase in unnecessary medication adjustments and referrals, prompting higher risk for adverse events. Furthermore, in patients with symptoms caused by drug-drug interactions (DDI), physicians only identified DDIs in 13% of patients. Finally, in patients who have disease progression despite adherence to medication and lack of DDIs, physicians continued with the patients’ current medication despite worsening disease.

This amendment allows us to ask a new set of primary care providers (PCP) that are particularly focused on chronic disease management, if they can change their practice after introducing them to the CDMT. VillageMD is a rapidly growing group of highly coordinated and aligned PCPs who excel in care of patients with multiple medical conditions. For VillageMD, findings from this study would represent a significant opportunity to improve their industry leading care services to better address medication non-adherence, check for DDIs, and improving care for patients who have progressive disease. QURE, under Aegis’s sponsorship and with VillageMD’s participation, will carry out a randomized control clinical trial among their VillageMD primary care providers.

|             |                                                                                                                                                |                       |
|-------------|------------------------------------------------------------------------------------------------------------------------------------------------|-----------------------|
|             | Clinical Study Protocol                                                                                                                 |                       |
|             | Title: Measuring the Clinical Utility of Aegis's Chronic Disease Management Test among VillageMD Providers: A CPV® Randomized Controlled Trial |                       |
| Supersedes: | Document Number:                                                                                                                               |                       |
|             | Effective Date:                                                                                                                                | Page: 14 of 25 |

QURE Village extends the findings from QURE 3 by measuring the change in clinical practice using CPVs® at a specific, targeted primary care provider network. We will look for the same changes we found in QURE 3 to determine the impact of the CDMT on clinical decisions and patient outcomes at VillageMD.

QURE Healthcare is a team of clinicians and researchers that conducts randomized-controlled trials using **Clinical Performance and Value (CPV®) patient simulations to generate high quality clinical utility evidence**. CPVs® are QURE's scientifically-validated measurement tool, first described in *JAMA*, 2000 and now used in scores of scientific investigations. In this research and derivative peer-reviewed publications, QURE's CPV® studies efficiently measure clinical practice patterns among active providers to determine if there is value of new technologies to payers.

QURE's CPVs® are a unique and scalable tool that standardizes practice measurement by having all providers care for the same (virtual) patient (*Annals of Int Med*, 2004). With all providers taking care of the same patients, QURE generates unbiased data that yields powerful insights into clinical decision making and how these decisions change with the introduction of a new product or solution (*Health Policy and Planning*, 2009). Data from the CPVs® can quickly demonstrate the clinical utility of a solution, be published in the peer-reviewed literature, and positively impact coverage and reimbursement decisions (*PLoS One*, 2013 and 2016). QURE CPVs® do this at a fraction of the time and cost of other data studies.

QURE will generate unbiased clinical utility evidence experimentally for VillageMD, using the validated CPV® randomized-controlled trial (RCT) approach. More specifically, QURE will demonstrate in the study how the Chronic Disease Management Test results change clinical decisions made by practicing primary care providers and how these changes align with evidence-based care options for patients.

A key element in determining clinical utility is determining the use cases where the Chronic Disease Management Test adds the most value. Because the clinical presentation and course for each CPV® patient can be precisely customized, QURE's validated patient simulation approach is uniquely positioned to explore multiple use cases and quantify the impact of the Chronic Disease Management Test within specific use cases. These cases can be strategically crafted to provide Aegis repeated opportunity to gather data on the use cases of most value for strategic, regulatory, and educational purposes. Based on the results of QURE 3, QURE will update the cases to present a new set of patients to the VillageMD providers.

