## Study Design

The study is a prospective randomized cohort two-arm trial with six steps:

- 1) Enrollment: The study will enroll an estimated 166 practicing primary care providers, who practice at VillageMD clinics. An eligibility screener will be used to screen for eligibility (attached as Appendix A).
- 2) Provider survey: Once providers are enrolled in the study, they will be asked to complete an item questionnaire describing their practice, professional background and confidence in treating patients with cardiometabolic conditions.
- 3) Randomization: The 166 VillageMD providers will be randomized into two equally- sized arms: control group and intervention group.
- 4) CPVs® (First Round): Providers in both groups will complete three CPV® patient vignettes. Cases will be identical across the intervention and control arms. Cases are interactive and are presented on an online platform that is accessible via unique weblinks and any internet-connected computer.
- 5) Intervention education: For the intervention group, providers will receive educational materials describing the clinical validation and use cases of the Chronic Disease Management Test. The education materials are an orientation to the test, its use, the results directed to the participants that will adopt the CDMT (e.g., introduction slide deck, fact sheet, and/or case studies)
- 6) CPVs® (Second Round): All participating providers will then be asked to complete three additional CPV® patient simulations. The cases are again given to the doctors in a random order.

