## 2.1 Study Instruments

There are two data collection instruments: 1) the provider questionnaire; and 2) the CPV® simulated patient cases.

The online provider questionnaire consists of 10-15 questions to better understand provider demographics, training and practice environment. It will be administered once, upon enrollment into the study.

The CPV® cases will be designed to simulate typical patients with chronic cardiometabolic conditions and polypharmacy. In each case, providers will care for the simulated patient by indicating their preferred course of action to work- up, assess, and manage these patients. Providers will complete the cases in random order to cancel out any learning effects (which are known to be small), and only the intervention group will receive CDMT results at the appropriate point in each round 2 CPV® case whether they select it or not. All told, nine cases

|             |                                                                                                                                                |                       |
|-------------|------------------------------------------------------------------------------------------------------------------------------------------------|-----------------------|
|             | Clinical Study Protocol                                                                                                                 |                       |
|             | Title: Measuring the Clinical Utility of Aegis's Chronic Disease Management Test among VillageMD Providers: A CPV® Randomized Controlled Trial |                       |
| Supersedes: | Document Number:                                                                                                                               |                       |
|             | Effective Date:                                                                                                                                | Page: 16 of 25 |

will be developed, and any given provider will randomly be assigned to two rounds of three cases. Intervention will occur between the two rounds.

CPV® vignettes will be designed based on a 3 x 3 matrix of chronic cardiometabolic diseases and common drivers for non-adherence and potential drug-drug interactions.

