##### *Longitudinal Data Analysis*

Primary Outcome Variables:

- Baseline variation in care among providers using standard of care tools, as measured by CPV® patient simulations
- In the intervention group, change in the overall and the diagnostic and treatment evidence-based quality scores and reductions in variation when caring for the CPV® simulated patient with the introduction of CDMT testing.

|             |                                                                                                                                                |                       |
|-------------|------------------------------------------------------------------------------------------------------------------------------------------------|-----------------------|
|             | Clinical Study Protocol                                                                                                                 |                       |
|             | Title: Measuring the Clinical Utility of Aegis’s Chronic Disease Management Test among VillageMD Providers: A CPV® Randomized Controlled Trial |                       |
| Supersedes: | Document Number:                                                                                                                               |                       |
|             | Effective Date:                                                                                                                                | Page: 22 of 25 |

- Changes in evidence-based management medication decisions (treatment) based on patient’s CDMT result.
- Distinguishing between medication non-adherence, DDI, and full compliance with suboptimal medication treatment (inadequate dosing vs. ineffective medication).
- Change in cost of chronic disease-related care. (This cost is modeled in part by measuring differential rates of work up/interventions/levels of care selected by each arm and multiplying by average Medicare reimbursement rates for these workups/interventions/ levels of care, and/or by modeling the incidence of expected complications and calculating associated costs per above).
- Difference in the above cost and clinical quality metrics and cost measures by three different use case types.

Secondary Outcome Variables:

- Calculation of the change in the expected cost and clinical quality metrics for each type simulated patient case (use case).

Main Explanatory Variable:

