- Intervention status (exposure to intervention)

We will control for all potential confounders, including:

- Age
- Gender
- Years in practice
- Practice location
- Type of location (urban/suburban vs. rural)
- Weekly hours in clinical practice
- Number of providers in practice
- Avg. type of coverage of patients (Medicare, Medicaid, commercial, etc.)
- Participation in care quality incentive programs
- Percentage of patients that have chronic cardiometabolic disease

We will model CPV® scores as a continuous outcome variable in a multiple linear regression model, which controls for all potential confounders listed above.

Our regression model is as follows, where CPV® is the score for each provider and INTERV indicates intervention group and CASE indicates the order in which the provider took the case (first, second, third, fourth).

|             |                                                                                                                                                |                       |
|-------------|------------------------------------------------------------------------------------------------------------------------------------------------|-----------------------|
|             | Clinical Study Protocol                                                                                                                 |                       |
|             | Title: Measuring the Clinical Utility of Aegis’s Chronic Disease Management Test among VillageMD Providers: A CPV® Randomized Controlled Trial |                       |
| Supersedes: | Document Number:                                                                                                                               |                       |
|             | Effective Date:                                                                                                                                | Page: 23 of 25 |

$$Y_{it} = \text{CPV}^{\circledR} \text{ score of provider } i, \text{ at time } t$$

$$Y_{it} \sim \text{Normal}(\mu_{ijt}, \sigma^2)$$

$$\mu_{ijt} = \beta_0 + \beta_1 \text{CASE} + \beta_2 \text{INTERV} + \beta_3 \text{CASE} \times \text{INTERV} + \text{provider-practice variables}$$

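### Each provider draws three of nine vignettes per round and the stated model has no vignette term, so baseline variation among providers absorbs differences in vignette difficulty

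*Protocol*

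**What the plan says.** Section 1 (Background Information and Rationale) says that the instrument "standardizes practice measurement by having all providers care for the same (virtual) patient", and draws from this: "With all providers taking care of the same patients, QURE generates unbiased data".

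Section 2.1 (Study Instruments) describes a different arrangement. "CPV® vignettes will be designed based on a 3 x 3 matrix of chronic cardiometabolic diseases" crossed with three mechanisms: non-adherence, drug interaction, and adherence without interaction. Of these nine cases, "any given provider will randomly be assigned to two rounds of three cases". No rule is given that a provider receives one case per disease or one per mechanism.

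The Synopsis (Study Design, step 4) and Section 2 add: "Cases will be identical across the intervention and control arms".

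Under Longitudinal Data Analysis in Section 8.b, the first primary outcome is "Baseline variation in care among providers using standard of care tools, as measured by CPV® patient simulations". The regression that follows contains CASE, INTERV, their product and provider-practice variables, where "CASE indicates the order in which the provider took the case (first, second, third, fourth"). The adjustment list opens with "We will control for all potential confounders, including" and names only provider and practice characteristics, including patient mix.

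**The concern.** If every provider treated the same three patients, case difficulty would shift all provider means equally and would not add to the spread between them. Once providers hold different sets, a provider who drew three hard vignettes scores lower than an equally skilled colleague who drew three easy ones. That gap then appears as variation in care.

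The outcome is a spread, so randomising the cases does not cancel this effect. Random allocation of cases balances difficulty between arms on average, but it still adds variance among individuals. The added part is never negative, so it pushes toward the sponsor's expectation of high unwarranted variation. Objective 1 depends on this quantity, as do the first three hypotheses in the Synopsis and the first two in Section 8.a.

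**Working it through.** **Inputs from the protocol.** Nine vignettes in a 3 x 3 layout and three per provider per round (Section 2.1). 166 recruited, 83 per arm, with 75 per arm expected after 10% attrition (Synopsis, Sample Size). The attrition figure reproduces: 83 x 0.9 = 74.7. With 150 completers, each vignette is seen in round 1 by about 150 x 3/9 = 50 providers.

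**Inputs assumed, because the protocol gives no score SDs.** Provider SD s_p = 4, 6 or 8 points; residual SD s_e = 8; between-vignette SD S_v = 3, 5 or 8 (n-1 divisor over the nine).

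**Overlap of case sets under unrestricted draws.**
- Possible sets: C(9,3) = 84.
- Expected number of shared cases for two providers: 3 x 3/9 = 1.
- Same set: 1/84 = 1.2%.
- No shared case: C(6,3)/84 = 20/84 = 23.8%.

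**Variance of a provider's three-case baseline mean.**
- Without the case draw: s_p² + s_e²/3.
- Added by drawing 3 of 9 without replacement: (S_v²/3)(1 - 3/9) = 2S_v²/9, which is 2.00, 5.56 and 14.22 for S_v = 3, 5 and 8.

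| s_p | S_v | without draw | with draw | share due to draw | SD inflation |
|---|---|---|---|---|---|
| 8 | 3 | 64 + 21.33 = 85.33 | 87.33 | 2.00/87.33 = 2.3% | sqrt(87.33/85.33) - 1 = 1.2% |
| 6 | 5 | 36 + 21.33 = 57.33 | 62.89 | 5.56/62.89 = 8.8% | sqrt(62.89/57.33) - 1 = 4.7% |
| 4 | 8 | 16 + 21.33 = 37.33 | 51.56 | 14.22/51.56 = 27.6% | sqrt(51.56/37.33) - 1 = 17.5% |

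The first and last rows are the extremes over the nine settings. With S_v = 0 the added part is zero.

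**Does a vignette term remove it?** A simulation with 150 providers, s_e = 8 and s_p = 5 gave an SD of provider means of 6.81, 7.22 and 8.30 at S_v = 0, 5 and 10 without the term. With a nine-level vignette term it gave 6.84, 6.83 and 6.86. The excess disappears.

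**If each provider received one case per disease and per mechanism.** There would be 3! = 6 possible sets. Difficulty that follows disease or mechanism would then cancel from every provider's mean, and only vignette-specific departures would remain. The added variance becomes (sum of squared departures)/18. If difficulty lies wholly in disease and mechanism, this is zero. If it has no such pattern, the departures carry 4 of the 8 degrees of freedom, giving 4S_v²/18 = 2S_v²/9, the same as under unrestricted draws. The simulation agrees: 7.21 against 7.22 at S_v = 5, with s_p = 5. Such a scheme therefore helps to the extent that difficulty follows the two design factors.

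**The case against.** The strongest reply is that the protocol gives no formula for baseline variation. The written regression is for mean scores, and the estimator for a descriptive spread is commonly left to a statistical analysis plan. A calculation within vignette would avoid the problem. This stands as far as it goes: a reader might infer that the plan is certain to count vignette differences as provider differences, and the text does not establish that. The protocol does state its adjustments, however, and its one case variable is order. The split by three use-case types does not fill the gap. If the types are the mechanisms, each still pools three disease vignettes.

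Four further points limit the concern.
- A reader might infer that the treatment comparison is biased. It is not: cases are assigned at random, so difficulty is balanced in expectation and only adds noise.
- A reader might take the statement that cases are identical across arms as a second error. It speaks of arms and is true when both arms draw from one bank, so the Synopsis step and Section 2 need no correction.
- A reader might measure the effect on individual scores, for example sqrt(16+64+64) = 12.0 against sqrt(16+64) = 8.9, an excess of 34%. That excess comes from pooling over cases, and most of it would remain if everyone took the same three. The provider mean is the quantity that matches the concern.
- The 1.2% and 23.8% assume unrestricted draws, which the text neither states nor excludes.

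It is also fair that the sentence in Section 1 is a general description of the tool, and that no threshold is set for high variation, so no formal test changes.

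**Conclusion.** The point holds in a limited form. The premise in Section 1 does not describe the design in Section 2.1, and the stated adjustments omit vignette identity. A between-provider spread taken with those adjustments alone is biased upward unless the nine vignettes are equally hard, which is unlikely given three disease groups, three mechanisms and a hypothesis that the test's utility differs by use case.

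The size depends on SDs that the protocol does not give. Over the assumed range it is about 2% to 28% of the variance of provider baseline means and about 1% to 17.5% of their SD, under unrestricted draws. It would be smaller if sets were balanced over disease and mechanism and difficulty mainly followed those factors. This should be put right because it affects the first-listed primary outcome. It does not call the arm comparison into question.

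**What to change.** 1. In the Section 8.b model, add vignette identity as a nine-level fixed effect beside case order.
2. Define baseline variation in one of two ways. One is the spread of round 1 scores within each vignette, among about 50 providers per case, averaged over the nine. The other is the between-provider variance from the model with the vignette effect and a provider-level random term, which also separates residual noise.
3. In Section 2.1, state how the three cases per round are drawn, including whether each set is balanced over disease and mechanism.
4. In Section 1, say that all providers draw from a common bank of nine cases.

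The cost is wording, one model term and one table. No new data or change to recruitment is needed.
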